### Interventions

#### Explanation for the choice of comparators

Exercise therapy is currently the main treatment approach for SP. From the perspectives of traditional Chinese medicine theory and modern medical research, acupuncture has the efficacy of promoting muscle growth. Then, will combining acupuncture with other mainstream therapies for SP further enhance the curative effect? Does acupuncture treatment for SP have a placebo effect? What are the specific mechanisms by which acupuncture improves SP? How effective is acupuncture specifically in terms of indicators such as muscle strength, muscle mass, and muscle function? We still lack strong clinical evidence in these aspects. Therefore, we have designed sham acupuncture combined with exercise therapy as the control group.

#### Intervention description

Eligible subjects will be randomly assigned to two parallel groups.

#### Acupuncture group treatment protocol

**Acupuncture:** For the selection of acupoints, bilateral Zusanli (ST36), Taixi (KI3), Sanyinjiao (SP6), Quchi (LI11), and Hegu (LI4) were selected (referring to the "Three-needle Therapy" published by China Medical Science Press [28] and the "Clinical Rehabilitation" published by People's Health Publishing House [29]). The location of these acupuncture points adheres to the Chinese national meridian point standard (GB/T 12,346 - 2021) [30].(1)ST36: It is situated on the lateral side of the lower leg, 3 cun (a traditional Chinese unit of length) distal to Dubi (the lateral patellar fossa), and approximately one fingerbreadth (equivalent to the width of the middle finger) lateral to the anterior border of the tibia;(2)KI3: Located in the ankle region, it lies in the depression between the tip of the medial malleolus and the Achilles tendon;(3)SP6: Positioned on the medial side of the lower leg, it is 3 cun proximal to the tip of the medial malleolus and at the posterior border of the medial aspect of the tibia;(4)LI11: When the elbow is flexed at a right angle, it can be found at the midpoint of the line connecting the lateral end of the elbow crease and the lateral epicondyle of the humerus;(5)LI4: It is located between the first and second metacarpal bones on the dorsum of the hand, precisely at the midpoint on the radial side of the second metacarpal bone. Fig. 3 depicts the positions of these acupoints;

**Fig. 3 fig0003:**
[figure not shown]
Diagram of acupoint locations.

Operation Method: Patients are required to lie in the supine position with their elbows bent and placed over the chest. The acupuncturist first disinfects their hands thoroughly and then conducts local disinfection of the selected acupoints using 75 % medical alcohol. A 0.30 mm × 40 mm needle is used to puncture the aforementioned points directly. The needling depth ranges from 20 to 30 mm . The tonifying needling technique is adopted for needle manipulation. Once the De-qi sensation is achieved, the needle is retained for 30 min. Needle manipulation is performed every 10 min (by reinforcing the lifting-thrusting and twirling maneuvers of the needle). After 30 min, the needle is removed. All procedures must be carried out in strict accordance with the standard operating procedures.

**Exercise Therapy:** The use of elastic bands for resistance exercise, along with the exclusion of inappropriate exercise factors, forms the basis for guiding patients to undertake exercise therapy with Thera-band elastic bands. These elastic bands feature different resistance levels denoted by various colors. Teal, yellow, or red bands, which are suitable for the elderly, are selected. Each exercise session consists of a 10-minute warm-up and a 15 - to 30-minute resistance exercise phase [1,5,31].

**Exercise Movements:**
(1)Seated Elastic Band Chest Expansion (Targeting the Triceps Brachii and Deltoid Muscles). As shown in ① of Fig. 4, the patient sits upright and grasps the ends of the elastic band placed in front of the chest with both hands. Against the resistance of the elastic band, the patient performs chest expansion movements. One set comprises 10 repetitions. A total of three sets are carried out, with a one-minute rest interval between each set.

**Fig. 4 fig0004:**
[figure not shown]
Illustration of exercise therapy movements.(2)Seated Elastic Band Chest Push (Targeting the Triceps Brachii and Pectoralis Major). In ② of Fig. 4, the patient is seated. With the elastic band looped around the upper back and held by both hands, the upper limbs execute forward thrusting motions while countering the resistance of the elastic band. Each set contains 10 repetitions. Three sets are performed in total, with a one-minute rest between sets.(3)Seated Elastic Band Biceps Curls (Targeting the Biceps). In ③ of Fig. 4, the patient holds both ends of the elastic band with both hands while the doctor helps to fix the middle part of the elastic band under the patient's feet. Subsequently, the patient conducts elbow flexion movements against the resistance of the elastic band. One set has 10 repetitions. A total of three sets are completed, with a one-minute rest between sets.(4)Seated Unilateral Stirrups (Targeting the Quadriceps and Gluteus Maximus). As depicted in ④ of Fig. 4, the patient takes a sitting position. The doctor helps the patient to fasten one end of the elastic band to the ground and loops the other end around the patient's ankle joint. Then, the patient performs knee flexion and extension movements against the resistance of the elastic band, alternating between the two lower limbs. Each set involves 10 repetitions. Three sets are carried out in total, with a one-minute rest between sets.(5)Seated Hip External Rotation (Targeting the Deep External Rotator Muscles around the Hip and the Gluteus Maximus). In ⑤ of Fig. 4, the patient is seated. The doctor loops the elastic band around the middle and lower parts of the patient's lower thighs. The patient then executes leg opening and closing movements while resisting the resistance of the elastic band. One set consists of 10 repetitions. Three sets are performed in total, with a one-minute rest between sets.

All the above-mentioned movements should be carried out under the supervision and assistance of the doctor.

Time Design: Upper and lower extremity training is alternated. Each exercise session lasts for 15 to 30 min. Initially, one movement training for each upper and lower extremity is carried out. Subsequently, the intensity is gradually increased according to individual differences. Each exercise session starts 1 to 2 h after a meal and is conducted every other day.

The treatment is administered on alternate days for 60 days, followed by a 90-day follow-up period.

#### Sham acupuncture group treatment protocol

In this group, the combination of sham acupuncture [32,33] and exercise therapy will be adopted. Sham acupuncture is performed by superficially pricking with a 0.30 mm × 40 mm needle at a location 2 cm away from the lateral edge of each acupoint selected for the acupuncture group (non-meridian and non-acupoint sites). No needle manipulation is involved, and the needle is retained for 30 min.

The exercise therapy in this group is identical to that in the acupuncture group. Similarly, the treatment and follow-up schedules are the same as those of the acupuncture group.

## Criteria for discontinuing or modifying allocated interventions

(1)In case of disease progression or the occurrence or potential occurrence of serious adverse events, the patient should withdraw from the clinical study. Those with aggravated conditions will be treated as invalid cases;(2)During the research process, if the subjects develop certain comorbidities, complications, or experience special physiological changes that may render them unfit to continue participating in the study, they should withdraw from the clinical study according to the doctor's judgment;(3)If the subjects are not satisfied with the efficacy of acupuncture or exercise therapy during the clinical study and are unwilling to continue participating in the clinical study, and they submit a request to withdraw from the clinical study to the attending doctor, they can withdraw from the study;(4)Subjects with poor compliance to acupuncture treatment, who violate the treatment protocol, or who receive other concurrent treatments that may affect the judgment of treatment efficacy.

### Strategies to improve adherence to interventions

First and foremost, the researchers from the three centers underwent rigorous training, enabling each of them to have a detailed understanding of all the study contents. The subjects participating in this research will receive free physical examinations, DXA examinations, QCT examinations, and relevant blood index examinations throughout the study. Considering that elderly patients with SP may have mobility issues, we will provide free pick-up and drop-off services for the subjects, subject to the approval of the ethics committee.

### Relevant concomitant care permitted or prohibited during the trial

Participants remain on their standard treatment and medication procedures throughout the study period, and clinicians are advised to manage participants in the usual manner subject to the caveats outlined above.

### Outcomes

#### Primary efficacy indicator

(1)The Appendicular Skeletal Muscle Mass: Both the Asian Working Group for Sarcopenia and the European Working Group on SP in Older People have mentioned that ASM measured by DXA is an important index for the diagnosis and efficacy evaluation of sarcopenia, which can directly reflect the changes in muscle mass [1,2]. A value of <7.0 kg/m^2^ in men and <5.4 kg/m^2^ in women is considered positive.(2)Handgrip strength: Handgrip strength is an important indicator for measuring muscle strength and one of the diagnostic criteria for SP. We use an electronic digital grip dynamometer. The patient stands with the elbow extended, and the dominant hand performs an isometric contraction with maximum force. The measurement is taken twice on the same hand with an interval of at least 15 s, and the maximum reading (kg) is selected. By referring to the recommendations of the Asian Working Group for Sarcopenia, we set the threshold as <28 kg for men and <18 kg for women [1].

#### Secondary outcome indicators

(1)The abdominal muscle area and muscle density at the L3 level measured by QCT: It is the clinical reference standards for measuring skeletal muscle mass and cross-sectional area. Since there is no unified threshold for evaluating SP using this method, we regard it as a secondary efficacy indicator. In this study, the thresholds recommended by Carey et al. through a large multi-center study are as follows: SMI ≤ 39 cm²/m² for women and SMI ≤ 50 cm²/m² for men [34,35].(2)6-meter walking speed: Walking speed is an important indicator for observing the limb function of SP patients. It can reflect patients' motor ability and systemic function, and is closely related to adverse outcomes of SP such as disability, cognitive impairment, hospitalization needs, falls, and mortality. In this protocol, the 6-meter walking speed test is adopted: Subjects are required to walk at their usual walking speed. During the assessment, when the subject's toes touch the 0-meter mark line, the timing starts from the first step beyond the 0-meter line and ends when the first step beyond the 6-meter line is taken. The corresponding time (seconds) is recorded. The test is conducted three times in total, with a 1-minute rest between each test, and the minimum value is taken as the test indicator [1].(3)FTSST: FTSST is also an indicator for observing patients' limb function. The subjects cross their hands in front of the chest, stand up from the chair until both lower limbs are fully extended, and then sit down. This is repeated continuously for 5 times, and the required time is calculated. The experiment is repeated 3 times, and the shortest time is recorded [1].(4)SPPB: SPPB mainly includes the assessment of three parts, namely gait speed, balance test, and chair stand test. The maximum score is 12 points. When the score is ≤ 8 points, it indicates poor physical performance. In terms of the gait speed test, methods such as the 4-meter usual walking speed test are usually adopted. The speed can be obtained by manually measuring the gait time with a stopwatch or using electronic devices. The balance test and chair stand test also have their own standard test procedures and scoring rules. These tests comprehensively reflect the physical performance status of an individual [1].(5)calf/waist/hip circumference: Calf/waist/hip circumference is an indirect indicator reflecting the muscle mass of patients and has certain value in observing the efficacy of SP. Using a non-elastic measuring tape, the circumferences are measured at the umbilical level, the most prominent part of the medial thigh muscles on the right side, and the maximum circumferences of both calves while the subject is standing and dressed [36,37].(6)Srum irisin/Myostatin: Myostatin is an actin secreted by skeletal muscle. The elevation of its plasma level can increase skeletal muscle fibrosis and lead to muscle atrophy. It can reduce skeletal muscle mass by regulating the division cycle of myoblasts and the expression of myogenic regulatory factors, ultimately inducing SP [38,39].Furthermore, studies have indicated that Myostatin, together with LIF (Leukemia Inhibitory Factor), IL-6 (Interleukin-6), and IL-7 (Interleukin-7), jointly participates in muscle hypertrophy and myogenesis. This finding serves to demonstrate that Myostatin plays a role in the growth and development of skeletal muscle itself and exerts a significant impact on local muscle function [40]. Irisin can alleviate the negative impact of Myostatin on musculoskeletal metabolism. The two regulate each other to balance skeletal muscle mass [41,42].Irisin is dependent on PGC-1α (Peroxisome Proliferator-Activated Receptor γ Coactivator 1α), whose core function is to drive brown-fat-like development. The primary role of brown adipose tissue is to consume energy through thermogenesis; thus, Irisin may hold significant implications for energy metabolism, particularly in obesity-related metabolic regulation. This underscores the impact of skeletal muscle—as a secretory organ—on systemic metabolism [40]. Daniel de Luis et al. have indicated that Irisin levels were significantly lower in patients with sarcopenia than in non-sarcopenic individuals; furthermore, higher Irisin levels were associated with a 61 % reduction in the risk of sarcopenia, and Irisin levels showed a positive correlation with AMSI. In contrast, Myostatin levels were negatively correlated with muscle mass, and Myostatin levels were 2.3-fold higher in elderly patients with sarcopenia [43]. Collectively, through the regulation of energy metabolism, the balance of muscle anabolism/catabolism, and the bone-muscle crosstalk network, Irisin and Myostatin play a central role in sarcopenia. Therefore, we believe that serum irisin and serum Myostatin have the potential to be indicators of the efficacy of SP treatment and have included them in the indicators of this protocol. The levels of serum irisin and myostatin will be measured by the researchers using enzyme - linked immunosorbent assay (ELISA) kits.

In summary, the efficacy indicators included in our study can comprehensively observe the muscle mass, muscle strength, and limb function of the patients, Table 1 provides a detailed explanation of this.

**Table 1 tbl0001:** Table of efficacy indicators. (All abbreviations in the table are presented in "Abbreviations").

**No.**	**Indicators**	**Primary / Secondary**	**Method**	**Effect**	**Refs.**
1	ASM	Primary	DXA	Reflect the muscle mass	[1,2]
2	Handgrip strength	Primary	An electronic dial-type hand- held dynamometer is adopted	Reflect muscle strength	[1]
3	The abdominal muscle area and (1) density at the L3 level measured	Secondary	QCT	Reflect muscle mass and cross-sectional area	[34,35]
4	6-meter walking speed	Secondary	Timing of walking at an average gait speed	Reflect somatic function	[1]
5	FTSST	Secondary	Timing of the subjects' sit-to-stand movement	Reflect somatic function	[1]
6	SPPB	Secondary	Scale-based Examination	Reflect somatic function	[1]
7	calf/waist/hip circumference	Secondary	Measurement with a non-elastic tape measure	Indirectly reflect the muscle mass	[36,37]
8	Srum irisin/Myostatin	Secondary	Serum examination	Reflect the muscle growth from the perspectives of cellular and organismal metabolism	[17–25]

#### Safety indicators

General physical examination items consist of height, weight, and body mass index (BMI), among others. Laboratory tests involve routine blood tests, blood glucose level monitoring, liver and kidney function assessments, as well as electrocardiogram (ECG) examinations. Additionally, special attention will be paid to observing any possible adverse reactions. These may be classified into local skin reactions and systemic reactions. Local skin reactions might present as allergic or non-allergic dermatitis, characterized by symptoms such as papules, skin erythema, edema, pruritus, blisters, or desquamation. Local discomfort may manifest as soreness, numbness, distension, or pain. Moreover, local hemorrhage and bruising could occur. Systemic reactions may include injection sickness and other conditions.

### Participant timeline

**Table utbl0002:** 

	**STUDY PERIOD**					
	**Enrolment**		**Post-allocation**		**Follow-up**	
**TIMEPOINT****	-t_1_	0	t_1_	t_2_	t_3_	t_4_
**ENROLMENT:**						
**Eligibility screen**	X					
**Informed consent**	X					
**[information acquisition]**	X					
**Allocation**	X					
**INTERVENTIONS:**						
**[Acupuncture group(Acupuncture+Exercise)]**		↔				
**[Sham Acupuncture group(Sham Acupuncture+Exercise)]**		↔				
**ASSESSMENTS:**						
**[SARC-Calf]**	X		X	X	X	X
**[ASM]**	X			X		X
**[The abdominal muscle area and muscle density at the L3 level measured]**		X		X		X
**[Handgrip strength]**	X		X	X	X	X
**[6-meter walking speed]**	X		X	X	X	X
**[FTSST]**	X		X	X	X	X
**[SPPB]**	X		X	X	X	X
**[calf/waist/hip circumference]**		X	X	X	X	X
**[Srum irisin/Myostatin]**		X		X		X
**[routine blood test]**		X		X		X
**[blood glucose]**		X		X		X
**[hepatorenal function tests]**		X		X		X
**[ECG]**		X		X		X

**Specific Timepoints:**t_1_** represents the stage of recruitment and diagnostic screening; **0** represents the baseline; **t_1_** represents the Visit 1 (30 days after treatment); **t_2_** represents the Visit 2 (60 days after treatment); **t_3_** represents the Visit 3 (30 days after the end of treatment); **t_4_** represents the Visit 4 (60 days after the end of treatment).

(All abbreviations in the table are presented in "Abbreviations".)

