### Eligibility criteria

#### Diagnostic criteria

In this study, the diagnostic criteria were formulated with reference to Sarcopenia in Asia: consensus report of the Asian Working Group for sarcopenia, 2019 [1](1)Preliminary screening: SARC—CalF questionnaire: a SARC—CalF questionnaire≧11 is classified as a positive SP screen;(2)Muscle power: Handgrip strength <28 kg for men and <18 kg for women;(3)Muscle function: Utilizing 6-meter walking speed and FTSST, 6-meter walking speed <1.0 m/s and FTSST >12 s. *Or sppb*≦9 points;(4)Muscle mass: DXA: ASM, Males <7.0 kg/m^2^, females <5.4 kg/m^2^.

The above item (1) is the case finding session, and (1)(2)(4) are performed on the patient when the SARC—CalF questionnaire is screened positive.

Diagnosis of SP: Decreased skeletal muscle content (positive for item (4))+decreased muscle strength (positive for item (2)) or decreased trunk function (positive for item (3));

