#### Inclusion criteria

(1) Patients who meet the aforementioned diagnostic criteria. (2) Patients aged between 60 and 80 years old, regardless of gender. (3) Those who have agreed to participate in this study and have signed the informed consent form.

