### Data collection and management

#### Plans for assessment and collection of outcomes

The primary efficacy indicator are ASM and Handgrip strength. The secondary outcome indicators encompass the abdominal muscle area and muscle density at the level of the third lumbar vertebra, including the rectus abdominis, transverse abdominis, internal and external obliques, quadratus lumborum, psoas major, and paraspinal muscles, which are quantified via QCT. Also included are 6-meter walking speed, the score of the FTSST, the score of the SPPB, calf/waist/hip circumference, serum irisin/myostatin. Considering the radiation from imaging examinations and the pain caused to patients by blood tests, the frequency and time of observation for each indicator are not completely the same, as detailed in Table 2.

**Table 2 tbl0002:** Time schedule for data collection of each indicator. (All abbreviations in the table are presented in "Abbreviations").

**No.**	**Indicators**	**baseline**	**Visit 1 (30 days after treatment)**	**Visit 2 (60 days after treatment)**	**Visit 3 (30 days after the end of treatment)**	**Visit 4 (90 days after the end of treatment)**
**1**	SARC—Calf	**√**	**√**	**√**	**√**	**√**
**2**	ASM	**√**		**√**		**√**
**3**	The abdominal muscle area and muscle density at the L3 level measured	**√**		**√**		**√**
**4**	Handgrip strength	**√**	**√**	**√**	**√**	**√**
**5**	6-meter walking speed	**√**	**√**	**√**	**√**	**√**
**6**	FTSST	**√**	**√**	**√**	**√**	**√**
**7**	SPPB	**√**	**√**	**√**	**√**	**√**
**8**	calf/waist/hip circumference	**√**	**√**	**√**	**√**	**√**
**9**	Srum irisin/Myostatin	**√**		**√**		**√**
**10**	routine blood test	**√**		**√**		**√**
**11**	blood glucose	**√**		**√**		**√**
**12**	hepatorenal function tests	**√**		**√**		**√**
**13**	ECG	**√**		**√**		**√**

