### Statistical methods

#### Statistical methods for primary and secondary outcomes

The main efficacy indicators will be analyzed using both the full analysis set (FAS) and per protocol set (PPS). The other efficacy indicators will be analyzed via the FAS set, while the safety indicators will be analyzed with the safety set (SS). The baseline equilibrium analysis will also be carried out using the FAS set.

Statistical analysis encompasses statistical description and statistical inference. For the statistical description of quantitative indicators, it includes mean, standard deviation, median, minimum value, and maximum value. Qualitative indicators are depicted by frequency tables and constituent ratios. Statistical inference involves interval estimation and hypothesis testing. For quantitative indicators, their two-sided 95 % confidence intervals (CIs) will be estimated. Each efficacy indicator will undergo bilateral testing with a significance level of α = 5 %. The null hypothesis posits that there is no statistically significant difference between the test group and the control group, whereas the alternative hypothesis contends that there is a statistically significant difference between the two groups. When *p* < 0.05, the null hypothesis will be rejected, and the difference between the two groups is deemed statistically significant.

Regarding measurement data, normality analysis is performed first. All data conforming to normal distribution are expressed as mean ± standard deviation. For comparison within the same group before and after treatment, the paired *t*-test is utilized, and for comparison between groups, the independent samples *t*-test is employed. For non-normally distributed measurement data, the rank sum test is adopted. For non-graded data in count data, the chi-square or non-parametric test is used. For graded data, the Ridit test is applied. In a bilateral test, a P value <0.05 is considered as a statistically significant difference.

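### The pre-treatment reading of ASM, handgrip and the function tests is a screening value in one schedule and a baseline value in the other; if it is the value that admitted the patient, the planned within-arm before/after tests are inflated by regression to the mean

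*Protocol article*

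**What the plan says.** The Participant timeline has two pre-treatment columns. One "represents the stage of recruitment and diagnostic screening"; the other, column 0, "represents the baseline". SARC-CalF, ASM, handgrip, 6-metre speed, FTSST and SPPB carry their only pre-treatment mark in the screening column. L3 QCT, circumferences, irisin/myostatin, blood tests and ECG carry theirs in column 0. Allocation is marked in the screening column.

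Table 2, titled "Time schedule for data collection of each indicator", has no screening column. It ticks all 13 indicators under a single baseline column.

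The Diagnostic criteria set the cut-offs: "Handgrip strength <28 kg for men and <18 kg for women" for grip and "Males <7.0 kg/m^2^, females <5.4 kg/m^2" for muscle mass, with further limits for the function tests. Low muscle mass is required of everyone, together with either low grip or low function. The first inclusion criterion is "Patients who meet the aforementioned diagnostic criteria".

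The Statistical methods section plans two comparisons. "For comparison within the same group before and after treatment" a paired t-test is used, and between groups an independent-samples t-test, both two-sided at 5%.

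**The concern.** ASM and handgrip are the two primary outcomes, and both are also entry criteria. A patient whose screening value had to fall below a cut-off is, on average, below it partly through measurement error. A second reading tends to be higher without any treatment. If the screening value is the before value, that rise enters every within-arm paired test on ASM, grip and function and can look like improvement.

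The two schedules leave this open. Under the timeline, the before value of these measures is the selected one, while QCT, circumferences and biomarkers get a separate baseline reading. Under Table 2, the measures may be repeated at baseline, or the screening value may simply have been relabelled. In the second case the problem is the same. At stake are the meaning of change from baseline for both primaries and the error rate of the planned before/after tests.

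**Working it through.** The protocol gives no figure on this point to reproduce. The inputs it supplies are 120 patients per arm (Sequence generation), two-sided 5% testing (Statistical methods), the entry rule (Diagnostic criteria) and an SD of 0.80 kg/m² (Sample size). Test-retest correlation r, the grip-function correlation and the position of the screened population relative to the cut-off are not given; they are assumptions, shown as ranges.

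**1. Everyone selected on one variable.** Let c be the cut-off in SD units from the population mean and λ = φ(c)/Φ(c). With no true change:
- expected change = (1 − r) × SD × λ
- variance of change = [(1 − r)²(1 − cλ − λ²) + (1 − r²)] × SD²

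Example with c = 0 and r = 0.90: λ = 0.3989/0.5 = 0.798. The shift is 0.10 × 0.798 = 0.080 SD. The SD of change is √(0.01 × 0.363 + 0.19) = 0.440. The noncentrality is 0.080/0.440 × √120 = 1.99, so the paired t-test rejects in 50% of arms. At r = 0.95 it rejects in 28% and at r = 0.80 in 81%. With the mean 0.5 SD above the cut-off, the rates for r = 0.95, 0.90 and 0.80 are about 50%, 80% and 98%. With the mean 1 SD below the cut-off they are 8%, 11% and 17%.

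**2. Handgrip under the actual entry rule.** Grip is one branch of an either/or rule, so some patients enter with grip above the cut-off and their grip is not truncated. Simulated mean and SD of change, then the noncentral t with n = 120, give these false-positive rates per arm for r = 0.95 / 0.90 / 0.80:

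| Population grip mean relative to cut-off | Set A: grip-function correlation 0.3, 50% function-positive | Set B: correlation 0.4, about 35% function-positive |
|---|---|---|
| 1 SD below | 6 / 7 / 9% | 7 / 9 / 12% |
| at cut-off | 8 / 11 / 17% | 12 / 19 / 33% |
| 0.5 SD (A) or 0.4 SD (B) above | 7 / 9 / 14% | 12 / 18 / 31% |
| 0.8 SD above | 6 / 8 / 11% | 10 / 13 / 22% |

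The apparent gain behind these rates is 0.008 to 0.087 SD. With an assumed grip SD of 6 kg that is 0.008 × 6 = 0.05 kg to 0.087 × 6 = 0.52 kg. Low ASM is not modelled separately; it would act mainly by moving the grip mean, which the rows cover.

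**3. ASM.** Low ASM is required of everyone, so step 1 applies. With SD 0.80 kg/m² and the cut-off at the mean, the shift is 0.80 × 0.02 × 0.798 = 0.013 kg/m² at r = 0.98 and 0.80 × 0.05 × 0.798 = 0.032 kg/m² at r = 0.95. Against the planned difference of 0.68 kg/m² these are 0.013/0.68 = 2% and 0.032/0.68 = 5%. The false-positive rates are 14% and 28%, because a highly repeatable measure also makes the paired test sensitive to a small shift. At r = 0.80, which would be poor repeatability for DXA, the shift would be 0.128 kg/m².

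**4. Checks with selection on one variable, cut-off at the mean, 4000 simulated trials.** With a separate reading after screening as the before value, the paired test rejects at 4.9% to 5.2%. The between-arm test of change, still taken from the screening value, rejects at 4.8% to 5.4%.

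**The case against.** The strongest reply is that this is mostly labelling. The timeline puts the screening and baseline columns under one enrolment heading, each schedule shows one pre-treatment reading per indicator, and Table 2's baseline can be read as that enrolment period. That reading is possible, but it makes the selected value the before value, which is the case that inflates the paired tests. The ambiguity therefore stands.

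Several stronger readings are tempting, and the documents do not support them:
- **The primary comparison is biased.** It is not. Both randomised arms regress equally, and the superiority hypotheses are stated between groups.
- **The false-positive rate is 28% to over 90%.** That needs every patient to enter through grip, with the population mean at or above the cut-off. The entry rule admits patients on function instead, and a mean below the cut-off is plausible after positive SARC-CalF screening.
- **Both arms would be declared improved.** The rates are per arm. At 31% per arm, both would be significant in about 0.31 × 0.31 = 10% of trials.
- **Within-arm gains would be reported as proof of efficacy.** The article does not say so. Since both arms receive exercise, a within-arm gain could not isolate acupuncture whichever reading came first.
- **Centres will record different before values.** This is conjecture. The article points to Table 2 for observation times and describes training across the three centres.

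**Conclusion.** The point holds, with limited consequences. The two schedules conflict in the current text on the pre-treatment timing of both primaries and the function tests, and they must be reconciled. If the admitting value is the before value, the paired tests do not keep their 5% level. For grip under the stated entry rule, the rate runs from about 6% to a little over 30% per arm, assuming r of 0.80 to 0.95, a grip-function correlation of 0.3 to 0.4, 35% to 50% of screened patients function-positive, and a population mean from 1 SD below to 0.8 SD above the cut-off. To the extent that patients enter through function, the same effect falls on walking speed, FTSST or SPPB. For ASM the shift is small in kg/m² if DXA is highly repeatable. The harm is confined to the within-arm tests.

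**What to change.** 1. In Statistical methods, state that within-arm before/after tests on the variables used for selection (ASM, grip, 6-metre speed, FTSST, SPPB) are descriptive, and that efficacy conclusions rest on the between-arm comparison. This costs one sentence.
2. Align the participant timeline with Table 2 by naming one pre-treatment reading per measure. For grip and the function tests, this is preferably a reading at time 0, with the screening reading used for eligibility only. Take it before allocation is released as well as before the first session: the timeline marks allocation in the screening column, the Blinding section says subjects and researchers are not blinded, and these tests depend on effort. The cost is a table correction and a few minutes of testing at a visit already scheduled for QCT, blood tests and circumferences.
3. For ASM, keep the single screening DXA, label it as the pre-treatment value in both tables, and apply rule 1 to it. This avoids a second exposure.

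The article reports that recruitment and treatment are under way and outcome assessment has not been reached, so the clarification can still be made. Patients already enrolled with only a screening reading can be covered by rule 1 alone.
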